### 2.12. Sample Size

As previously stated by the FDA and confirmed by the MCID recommended by Myles et al. [37], we set the margin of non-inferiority at 10 mm. Based on a 21.9 mm standard-deviation of the VAS score^38^ and assuming an alpha of 0.05, the minimum sample size required to achieve a power of 80% to reject the inferiority null hypothesis was 60 per group. Adding to that a 5% margin of estimated non-usable data the total number of subjects will be of 126.

Streff et al. [38] had a similar utilization of experimental pain in their study using a CPT on healthy subjects and a visual analog scale (VAS) to estimate pain. In the dataset they present, a standard deviation of 21.9 mm is calculated.

### 2.13. Statistical Analysis

We will perform the statistical analysis with alpha = 0.05. Unless stated otherwise, all tests will be bilateral. We will perform the tests with an Intention To Treat population: all participants will be analyzed in the group in which they were initially randomized.

Missing data on the primary endpoint will be imputed by multiple imputation if between 5% and 20% of the measurements are missing. If less than 5% are missing, we will not impute the missing data. If more than 20% of the data are missing, the results will be interpreted with caution. We will not perform missing data imputation on the other endpoints.

We will test the non-inferiority of the Educated Placebo compared to the Conventional Placebo using the unilateral 95% confidence interval of the difference of the pain intensity. The non-inferiority margin is set to 10 mm on the VAS. We will estimate the confidence interval by linear regression. The linear regression will account for the pain intensity without placebo and the sequence of the CPTs. As an Intention to Treat analysis can be biased when evaluating a non-inferiority [39], we will also test the non-inferiority with a per protocol analysis: subjects will be included in the group only if there were no deviations from the protocol. If the results of the two analysis are discordant, we will interpret the results with caution.

We will also test the superiority of the Conventional Placebo compared to no-treatment by a cross-over ANOVA. Similarly, we will test the superiority of the Educated Placebo compared to no-treatment by a cross-over ANOVA. We will test the other between group differences by Student’s *t*-test for two independent samples.

We will test the effect of the education in the Educated Placebo group by Student’s *t*-test for paired samples comparing the knowledge about Placebo before and after the educational video.

This study will allow us to rule on the non-inferiority of an educated placebo compared to conventional placebo in the context of an acute painful stimulation. We have highlighted the need to study the different determinants increasing the placebo effect, and in particular the understanding of underlying placebo mechanisms. This study is the first step in a series of research works that could allow an ethical use of placebo in clinical practice.

Analysis will be conducted on Stata software, version 15 (StataCorp LLC, College Station, TX, USA) or higher.

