## 2. Materials and Methods

### 2.1. Objectives

The main objective of this study is to investigate whether or not an educated placebo is non-inferior to a deceptive placebo treatment on treating acute pain intensity. Secondary objectives of the study include verifying the superiority of both placebo treatments with a no-treatment Cold Pressor Test (CPT). We will also assess the effect of both placebo treatments on anxiety. This study also aims to measure whether or not the educational video was effective in transmitting knowledge about the placebo effect.

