### 4.2. Future OLP Research

As stated during the 2019 SIPS conference, future research on open-label placebo will be faced with several challenges in order to justify a potential use in a clinical setting. Among these challenges is the investigation of the mechanisms behind open-label placebos’ efficacy and what triggers exist that modulate this efficacy. Current hypotheses revolve around the patient–therapist relationship, the treatment in itself and/or the rationale given to the patients. This study will allow for gaining insight regarding the latter. The modalities of the educational intervention, explained and argued in the previous subsection, will allow for interesting discussion once the results are obtained.

Another challenge future research needs to take into account is to conduct investigations on subjects that are not healthy subjects. This protocol helps towards justifying the use of OLP with patients once used with healthy subjects with no risks and shows potential benefits. At the time of conceptualization of this protocol, too few studies allowed for ethical justification of the use of OLP with patients.

One of the major difficulties in regard to OLP research is the difficulty in using control groups as a reference. Past studies have used no treatment or treatment as usual groups as controls. This study suggests an original methodology with two parallel groups as well as an intra-group control. This allows for intra-subject control as well as comparison between a no treatment condition and a treatment condition. Of course, this means that the statistical analysis must show, in order to conclude a non-inferiority with clinical relevance, that both the deceptive placebo and the open-label placebo are statistically superior to the no treatment condition while also finding the open-label placebo condition to be non-inferior to the deceptive placebo. This methodological challenge of having a valid control group seems to justify the necessity in publishing protocols allowing for a detailed peer-review process. This allows going in-depth into the process used to elicit a placebo response as well as give a detailed account of the context present during the inclusions.

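### Section 4.2 makes superiority of both placebos over no treatment a condition for concluding clinically relevant non-inferiority, but Sections 2.1, 2.12 and 2.13 do not carry that condition

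*Protocol article*

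**What the plan says.** **Section 2.13** bases the primary test on the interval: "We will test the non-inferiority of the Educated Placebo compared to the Conventional Placebo using the unilateral 95% confidence interval of the difference" in pain intensity. The interval comes from a linear regression that adjusts for control-CPT pain and CPT sequence. The section then adds a cross-over ANOVA of each placebo against no treatment as further tests. The only qualifier on the non-inferiority result is that discordant intention-to-treat and per-protocol analyses call for caution.

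**Section 2.1** makes superiority over no treatment a secondary objective, and **Section 2.3** makes placebo versus no treatment the main secondary end point.

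**Section 2.12** sizes the trial for non-inferiority only: "the minimum sample size required to achieve a power of 80% to reject the inferiority null hypothesis was 60 per group". On the margin it says "we set the margin of non-inferiority at 10 mm", justified as a minimal clinically important difference.

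**Section 4.2**, in the Discussion, says that a clinically relevant conclusion of non-inferiority requires the analysis to show "that both the deceptive placebo and the open-label placebo are statistically superior to the no treatment condition", in addition to non-inferiority of the open-label placebo.

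**The concern.** The article gives two accounts of what the primary conclusion needs. Read alone, 2.13 asks for one interval below 10 mm. Section 4.2 asks for that and two superiority results. If the interval clears 10 mm but one superiority test fails, two careful readers could report the same data differently.

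This matters more here than in a trial with an established active comparator. Both arms receive a cream with no active substance (2.6), so an effect of the comparator cannot be presumed. The margin is not tied to the size of the deceptive placebo's effect, and the article gives no figure for that effect. If it is below 10 mm, the margin is wide enough for all of it to be lost. If neither placebo does anything, the arms are equal and the interval will usually clear the margin.

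**Working it through.** **Inputs from the documents.** Margin 10 mm, SD 21.9 mm, alpha 0.05, 60 per group (2.12). One-sided 95% interval, adjustment for control-CPT pain, and two-sided tests unless stated otherwise (2.13).

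**Assumptions.** The article gives neither the placebo effects nor the correlation ρ between a subject's control and placebo scores. I use effects of 0 to 10 mm and ρ = 0.5 and 0.7.

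**Step 1: reproduce the sample size.**
n = 2 × 21.9² × (1.645 + 0.842)² / 10² = 59.3, so 60 per group. SE = 21.9 × √(2/60) = 4.00. Power = Φ(10/4.00 − 1.645) = 80.4%. Total = 120 × 1.05 = 126. The plan's figures reproduce for the non-inferiority test at one-sided 0.05.

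**Step 2: chance that the interval alone supports non-inferiority.**
Let δ be the true deficit of the educated placebo. P = Φ((10 − δ)/SE − 1.645). With adjustment, SE = 4.00 × √(1 − ρ²), which is 3.46 at ρ = 0.5 and 2.86 at ρ = 0.7. The educated placebo has no effect in any row.

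| Deceptive effect (= δ) | Unadjusted | Adjusted, ρ = 0.5 | Adjusted, ρ = 0.7 |
|---|---|---|---|
| 0 mm (neither works) | 80% | 89% | 97% |
| 5 mm | 35% | 42% | 54% |
| 8 mm | 13% | 14% | 17% |
| 10 mm | 5% | 5% | 5% |

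Example, 5 mm unadjusted: Φ(5/4.00 − 1.645) = Φ(−0.39) = 35%.

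**Step 3: the same cases under the three-test rule.**
An ineffective placebo is found superior with probability 2.5% (the favourable tail of a two-sided 5% test). If neither works, both superiority tests succeed with probability at most 0.025 × 0.025 = 0.06%. If only the deceptive placebo works, the joint probability cannot exceed 2.5%. In simulation it was about 2% or less.

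**Step 4: joint power when both placebos work equally (adjusted analysis).**
Per-arm superiority power = Φ(e/SEw − 1.96), where e is the effect and SEw = 21.9 × √(2(1 − ρ)/60), that is 2.83 at ρ = 0.5 and 2.19 at ρ = 0.7. The simulation used bivariate normal scores, paired t-tests in place of the cross-over ANOVA, and no period effects.

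| Effect in both arms | Superiority power per arm, ρ = 0.5 / 0.7 | Joint power, ρ = 0.5 / 0.7 |
|---|---|---|
| 5 mm | 42% / 63% | about 16% / 38% |
| 8 mm | 81% / 95% | about 58% / 87% |
| 10 mm | 94% / 99.5% | about 80% / 96% |

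Multiplying the two superiority powers by the non-inferiority power agrees to about one point. At 5 mm and ρ = 0.5, for example, 0.42 × 0.42 × 0.89 = 16%.

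**The case against.** The strongest reply is that the safeguard is already in the article. Section 4.2 states all three requirements in mandatory terms, 2.13 plans all three tests, and 2.3 ranks placebo versus no treatment as the main secondary end point. Section 2.13 never says that the interval alone settles the conclusion. Since 4.2 speaks of clinically relevant non-inferiority, 2.13 can be read as the test and 4.2 as its interpretation. A formal success rule might also stand in an analysis plan that is not shown.

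Much of this stands. A reader might infer that the plan has no protection against an inert comparator. It has, and the fault is that the protection sits in the Discussion and is not carried into the sections that define objective, size and analysis. The qualifier on clinical relevance leaves room for a plain non-inferiority claim under 2.13. A separate analysis plan does not remove the difference between two parts of this article.

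It is also fair that a true 5 mm deficit lies inside the margin, so rejecting a 10 mm deficit there is not a type I error of the planned test. The issue is what the result would be taken to mean.

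**Conclusion.** The point holds as a mismatch between 4.2 and Sections 2.1, 2.12 and 2.13, and it affects what the trial may conclude. The case that neither placebo works depends least on assumptions: about 80% unadjusted from the plan's own inputs, and 89–97% adjusted at ρ = 0.5–0.7, against 0.1% or less under the three-test rule. The case of an ineffective educated placebo beside an effective deceptive one depends on the unstated deceptive effect. It is a problem only below 10 mm, and by 10 mm the rate is the nominal 5%.

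Two stronger readings are not supported:

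- **That the stated 80% is wrong.** Section 2.12 attaches it only to rejecting inferiority, and it reproduces.
- **That the three-test rule must be underpowered.** Its power is unstated, not necessarily low. With the adjusted analysis of 2.13 it is about 80–96% at 10 mm, and it falls to about 16–38% only for an assumed 5 mm effect. Unadjusted figures would be lower but do not describe the planned analysis.

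**What to change.** 1. **Sections 2.1 and 2.13:** state that non-inferiority is concluded only if (a) the upper one-sided 95% limit for educated minus deceptive placebo is below 10 mm, (b) the deceptive placebo is superior to no treatment, and (c) the educated placebo is superior to no treatment. Say what will be reported if (a) holds and (b) or (c) fails. No alpha split is needed because all three must succeed.
2. **Section 2.12:** keep 80% as the power of (a) alone. Add the joint power of (a) to (c) over a stated range of placebo effects and within-subject correlations, using the adjusted analysis.
3. **Optional:** report the share of the deceptive effect that the educated placebo retains, with an interval. This ratio is unstable if the deceptive effect is small, so it should not be part of the success rule.

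The cost is wording, plus a stated joint power that may be less favourable than 80%. No new subjects or data are needed, because every subject already has a control CPT. The change should be made before the group codes are broken, so that the choice of rule cannot depend on the results.

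### The rule for discordant ITT and per-protocol results decides nothing, so it does not exclude a non-inferiority claim when ITT passes and per-protocol fails

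*Protocol article*

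**What the plan says.** Section 2.13 sets the analysis population: "We will perform the tests with an Intention To Treat population: all participants will be analyzed in the group in which they were initially randomized". Non-inferiority is judged "using the unilateral 95% confidence interval of the difference of the pain intensity", and "The non-inferiority margin is set to 10 mm on the VAS".

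The same section then qualifies the ITT analysis: "As an Intention to Treat analysis can be biased when evaluating a non-inferiority [39], we will also test the non-inferiority with a per protocol analysis". The per-protocol set is strict: "subjects will be included in the group only if there were no deviations from the protocol". For the case where the two analyses disagree, the whole instruction is: "If the results of the two analysis are discordant, we will interpret the results with caution".

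Section 4.2 adds conditions for a clinically relevant conclusion: superiority of each placebo over no treatment, on top of the non-inferiority result. The analysis has to show "that both the deceptive placebo and the open-label placebo are statistically superior to the no treatment condition while also finding the open-label placebo condition to" (the sentence goes on to state the non-inferiority requirement). No analysis population is named there.

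**The concern.** The per-protocol test is there for one reason, the authors' own statement that "an Intention to Treat analysis can be biased when evaluating a non-inferiority". A safeguard of this kind protects only if its failure has a consequence, and here it has none. The text does not say that both analyses must succeed, which of them prevails, or that disagreement means non-inferiority has not been shown.

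The case that matters is an ITT pass with a per-protocol failure. If deviations blunt a real difference between the arms, the ITT estimate moves towards zero, and in a non-inferiority trial that favours success. In this case the plan leaves the conclusion to judgement after the results are seen, although the Abstract and Section 2.13 both say that the study will settle the question of non-inferiority.

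This is more than a detail left to a fuller document. The article does state what happens under discordance, and what it states does not decide.

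**Working it through.** **Inputs from the article.** Margin 10 mm and one-sided 95% limit (Section 2.13). SD 21.9 mm, alpha 0.05, power 80%, 60 per group, 126 in total after a 5% allowance for non-usable data (Section 2.12).

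**Reproducing the plan's figure.** With a true difference of 0, n per group = 2 × 21.9² × (1.645 + 0.842)² / 10² ≈ 59.3, so 60. Then 120 × 1.05 = 126, or 63 per group. Both stated figures reproduce at one-sided 0.05. The point therefore concerns the decision rule and not the sample size arithmetic.

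**Assumptions that the article does not supply.** A share f of subjects in each arm deviates. Deviators show no difference between arms. Compliant subjects differ by exactly 10 mm, the boundary of inferiority. The gain from covariate adjustment is ignored.

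**ITT test alone.** The diluted difference is 10 × (1 − f). With 60 per group, SE = 21.9 × √(2/60) = 4.00, and

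P(ITT passes) = Φ((10 − 1.645 × 4.00 − 10(1 − f)) / 4.00).

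- f = 0: Φ(−1.645) = 5.0%
- f = 5% (9.5 mm): 6.4%
- f = 10% (9 mm): 8.2%
- f = 20% (8 mm): 12.6%

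With 63 per group the same formula gives 6.5%, 8.2% and 12.9%.

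**Both analyses together.** This was simulated with 200,000 runs, 63 per group and SD 21.9. The number of compliant subjects per group is rounded to a whole number, which explains small differences from the formula.

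| Deviators | Per-protocol n per group | False pass, ITT alone | False pass, both required | ITT passes, per-protocol fails |
|---|---|---|---|---|
| 5% | 60 | 6.4% | 4.6% | 1.8% |
| 10% | 57 | 8.0% | 4.4% | 3.6% |
| 20% | 50 | 13.2% | 4.5% | 8.7% |

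The last column is the outcome that the plan leaves open. Requiring both keeps the false-pass rate below 5% without any alpha adjustment, because the joint criterion cannot pass more often than the per-protocol test does.

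**When the true difference is 0.**

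| Deviators | Power, ITT alone | Power, both required | ITT passes, per-protocol fails |
|---|---|---|---|
| 5% | 82.1% | 78.8% | 3.3% |
| 10% | 82.1% | 76.6% | 5.4% |
| 20% | 82.0% | 71.5% | 10.5% |

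The unresolved outcome would therefore not be rare even if the two placebos were truly equal.

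**The case against.** A reader might infer three stronger things, none of which the article supports.

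- *That the protocol calls its own ITT analysis biased.* It says only that ITT can be biased in this setting.
- *That non-inferiority will be claimed on ITT alone.* Section 2.13 prespecifies both analyses and asks for caution if they disagree. It does not announce such a claim; it fails to exclude one.
- *That the real error rate exceeds 5%.* This needs deviations that dilute the contrast and also a claim made despite a failed per-protocol result. The article establishes neither.

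The dilution may also be small in this design. There is one supervised session (Section 2.2), the envelope is opened on site (Section 2.9), and the investigator applies the cream and gives the arm-specific statement in person (Section 2.10). Nothing is taken home. A lapse in water temperature or pause length may add noise without erasing the difference between arms. The 5% in Section 2.12 is the only comparable figure, and it refers to non-usable data rather than deviations. On the other hand, the procedure has many strict steps (Section 2.8) and the per-protocol set tolerates no deviation at all, so the two sets could still differ visibly.

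Section 4.2 is a further hurdle. The rates above are for the ITT non-inferiority test alone. The rate for the full conclusion cannot be higher and may be lower. Those conditions do not settle ITT against per-protocol.

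Finally, a per-protocol set excludes subjects after randomization and can itself be biased. Naming one analysis as decisive would also close the gap. This affects the choice of remedy; the need for a rule that decides still stands.

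**Conclusion.** The concern holds in a limited form. The discordance rule is stated but not binding, and nothing else in the article says which analysis governs the conclusion. The gap falls on the very case that the second analysis was added to cover.

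Its size is conditional. If ITT alone were used, the false-pass rate would be about 6.4% at 5% deviators, 8.2% at 10% and 12.6% at 20%, against a nominal 5%. These figures rest on assumed deviation shares and on a complete loss of the between-arm difference in deviators. In a single supervised session the lower end, or less, is plausible. They show what the open rule could permit and are not an estimate of this trial's error rate.

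**What to change.** Replace the sentence on discordant results with:

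> Non-inferiority will be concluded only if the upper one-sided 95% limit is below 10 mm in both the ITT and the per-protocol analysis; if they disagree, non-inferiority is not shown.

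This should be settled before the group codes are broken. It matches the all-must-hold logic that the authors already use in Section 4.2.

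The wording costs one sentence, but the loss of power should be stated openly. It is modest at 5% deviators and about ten percentage points at 20%, and in all three cases joint power falls below the planned 80%. The sponsor should restate power for the expected per-protocol size. As a guide, 60 compliant subjects per group give 80% for the per-protocol test alone. That means randomizing 60/0.90 ≈ 67 per group at 10% deviators, or 60/0.80 = 75 at 20%, and joint power would still be slightly lower. The gain from adjusting for pain without placebo may offset part of this, but the article gives no figure from which to calculate it.

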### 2.3. Assessment

The primary end point will be the difference in pain intensity, assessed on a 100-point visual analogue scale (VAS), between the educated OLP and the deceptive placebo treatments at the end of the placebo condition CPT. We have chosen pain intensity as opposed to pain threshold because it involves less motivational and cognitive components [33].

The main secondary end point will be, for each subject, the difference in pain intensity, also assessed by VAS, between open or deceptive placebo versus no-treatment control. Secondarily, a questionnaire (inspired by Hughes et al.’s data [34]) measuring knowledge regarding the placebo effect will be completed by all the subjects after the study and also before the educational video for the educated placebo group. In addition, all the subjects will complete another questionnaire about their perception of the investigators and of the study [35]. Blood pressure (BP) and heart rate (HR) values will be obtained before, during, and after each CPT by means of an automatic blood pressure monitor. Finally, subject’s anxiety will be evaluated through heart rate variability. Before the CPT treatment, an expectancy questionnaire will be used [36].

We expect to find a non-inferiority between both groups on the main end point. Considering the nature of the dependent variables and the choice of the painful stimulation, we expect a high interindividual variability. This has been limited as best as possible by the cross-over conducted in both arms of the study.

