### 2.8. CPT Procedure

Each volunteer will be initially subjected to a calibration test according to the CPT procedure and then to the experimental tests. After this, a debriefing and two questionnaires will conclude the inclusion.

Each CPT procedure is as follows. Every CPT is preceded by a 3 min monitored resting period where heart rate and respiratory rate are measured. Blood pressure is measured at the end of this 3 min baseline assessment. The hand and forearm temperature will be checked on both sides for reference. The non-dominant hand and distal third of the forearm will be immerged into the CPT at 1 °C +/− 1 °C. The forearm length submerged in the cold-water tank will be determined as follows: 1/3 of the distance between the ulnar styloid and the tip of the olecranon. The elbow will be placed on the outer rim of the water tank and the hand relaxed with no contact with the bottom of the tank.

For the calibration CPT, patients will be asked to record the intensity of their pain on the VAS every 5 s approximately. When the intensity exceeds 7/10 on the VAS, the subject will be told to remove his or her hand from the water. The time at which this event occurs will be referenced as (*t*). For both of the other CPTs, patients will be asked to keep the hand in the tank during (*t*) seconds and complete a VAS as soon as the hand is taken out of the water.

In between each CPT, a 20 min pause is mandatory and skin temperature is checked before the next CPT. If needed, a tank of warm water at approximately 25 °C can be used to warm up the hand until it reaches contralateral temperature.

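### The remaining between-arm comparisons, by default including HRV-based anxiety, heart rate and blood pressure, go to a two-sample t-test with no stated adjustment, which is valid but gives up precision

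*Protocol article*

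**What the plan says.** Among the secondary objectives, section 2.1 lists: "We will also assess the effect of both placebo treatments on anxiety". It comes directly after the objective of showing both placebos superior to a CPT without treatment.

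Section 2.3 evaluates anxiety through HRV and adds that "Blood pressure (BP) and heart rate (HR) values will be obtained before, during, and after each CPT". Under section 2.8, each CPT follows a 3 min "monitored resting period where heart rate and respiratory rate are measured", with BP taken at its end. Every participant also has a control CPT without cream, in random order with the placebo CPT (sections 2.2 and 2.10).

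Section 2.13 sets the general rules: "We will perform the statistical analysis with alpha = 0.05" and "Unless stated otherwise, all tests will be bilateral". It then names four kinds of analysis:

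- a linear regression for non-inferiority on pain, adjusted for pain without placebo and for CPT sequence;
- cross-over ANOVAs for each placebo against no treatment, with no outcome named;
- a paired t-test for knowledge before and after the video;
- for everything else between arms, "We will test the other between group differences by" an independent-samples t-test.

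Anxiety, HR and BP are not named in that section.

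**The concern.** HRV, HR and BP have no method of their own, so their between-arm comparison falls under the last item. Nothing there says that the test uses the resting values, the control CPT or the randomised sequence. The primary analysis of the same trial does adjust, and sections 2.3 and 4.1 say that wide differences between people are expected and count on the cross-over to limit their effect. A t-test on the placebo-CPT reading alone uses none of that. What is at stake is wider intervals than the data require.

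There is a second, smaller matter. The anxiety objective speaks of the effect of both placebos. A comparison of one placebo with the other does not measure either against no treatment. If both lowered anxiety equally, a null t-test could be misread as no effect on anxiety.

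**Working it through.** **The plan's own figure.** The only sample size stated is for pain (section 2.12): "we set the margin of non-inferiority at 10 mm", SD 21.9 mm, 80% power. The test is one-sided at 0.05, since section 2.13 tests "using the unilateral 95% confidence interval of the difference of the pain intensity".

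n = 2 × (1.645 + 0.842)² × (21.9/10)² = 59.3, so 60 per group, and 120 × 1.05 = 126. Both figures reproduce. The sample size is not at issue, and the article gives no SD or power for HRV, HR or BP.

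**Inputs for the secondary outcomes.**

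- n = 60 per group (section 2.12).
- Two-sided 0.05 (section 2.13).
- r, the correlation of the outcome with the participant's own resting value. This is an assumption, shown from 0.3 to 0.8.

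**Precision of the between-arm comparison.**

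- Adjustment multiplies the variance by 1 - r². The raw t-test therefore has 1/(1 - r²) times the adjusted variance, and 60 per arm work like 60/(1 - r²).
- The smallest difference detectable with 80% power is (1.960 + 0.842) × √(2/60) = 0.511 SD unadjusted, and 0.511 × √(1 - r²) adjusted.
- Power for a difference of 0.4 SD (chosen for illustration) is 59.1% unadjusted.

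| r (assumed) | 1 - r² | Variance ratio, raw to adjusted | 60 per arm work like | Detectable difference, adjusted (SD) | Power at 0.4 SD, adjusted |
|---|---|---|---|---|---|
| 0.3 | 0.91 | 1.10 | 66 | 0.488 | 63.2% |
| 0.5 | 0.75 | 1.33 | 80 | 0.443 | 71.6% |
| 0.8 | 0.36 | 2.78 | 167 | 0.307 | 95.5% |

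**If the t-test were run on changes from the resting value.** The article does not say whether it would be. The variance factor is then 2(1 - r): 1.4 at r = 0.3, 1.0 at r = 0.5 and 0.4 at r = 0.8. So changes are less precise than raw values at r = 0.3, equal at r = 0.5 and better at r = 0.8. The adjusted model is more precise at all three (0.91, 0.75 and 0.36).

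**What a between-arm test can show.** In a simulation of 20,000 trials, both placebos lowered anxiety by 0.5 SD against control, with within-person correlation 0.6 and 60 per arm (all assumed apart from n). The between-arm t-test rejected in 5.1% of trials on raw values and 5.3% on placebo-minus-control differences, which is its false-positive rate. The paired within-arm comparison rejected in 98.9%.

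**Which covariate.** The video is shown after calibration (section 2.10), so the resting value before the calibration CPT precedes the intervention. The control CPT comes after the video and, in one of the two sequences, after the placebo CPT, so its value could be affected by arm. The envelope is opened before calibration (section 2.9), so the resting value is recorded with the allocation known to the investigator, but before the group-specific information is given.

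**The case against.** The strongest reply is that the assignment to the t-test is inferred. Section 2.13 names neither anxiety, HR nor BP in that sentence. The cross-over ANOVA sentences are not limited to pain, and section 4.1 speaks of the cross-over as serving secondary endpoints in general. On that reading, the within-arm analysis of anxiety is already planned, and the t-test covers only the remaining contrasts between arms. The input to the t-test might also be a change score.

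Much of this stands. A reader might infer that the anxiety objective goes unanswered. The article does not support that, because it leaves open whether the cross-over ANOVA covers anxiety. The narrower reading is also possible: section 2.1 lists anxiety apart from superiority over no treatment, and section 2.3 ties the main secondary endpoint to the pain VAS. What remains is an ambiguity that one clause would settle.

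A second reply is that details for secondary outcomes belong in a full protocol or SAP that is not shown. That would answer silence, but the article is not silent: it fixes a t-test for the remaining between-arm comparisons, and it is that choice which can be improved.

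A third is that the t-test is valid and the gain rests on an assumed correlation. Both are true. There is no bias, and at r = 0.3 the gain is small.

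**Conclusion.** The point holds as one of efficiency and clarity on secondary outcomes. The stated between-arm test is valid, but on raw values it has 1.10 to 2.78 times the variance of an adjusted analysis for r from 0.3 to 0.8. That range rests on the assumed r and on the default reading that HRV, HR and BP fall under the t-test sentence. A comparison between arms alone does not measure each placebo against no treatment, and the text does not clearly say that the cross-over ANOVA does so for anxiety.

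The primary non-inferiority analysis, the sample size and the superiority conditions for pain do not depend on this.

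**What to change.** In section 2.13, or in the SAP:

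1. For HRV, HR and BP, replace the between-arm t-test by a linear model with arm, CPT sequence and the resting value recorded before the calibration CPT.
2. State that the within-arm cross-over ANOVA (placebo CPT against control CPT) also applies to the anxiety measure.

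The cost is a few lines of wording. For HR and BP the resting values are already scheduled. For HRV the article gives neither the index nor the timing, so the plan should confirm that HRV can be derived from the monitored rest before calibration. For the same reason, no transformation of HRV is recommended here.
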